### Setting

Data will be gathered in 18 Dutch hospitals, all of which are at the beginning stages of the implementation of the Frail Elderly Project at the start of the study (self-reported status). These 18 hospitals include two university hospitals, five teaching hospitals, and eleven general hospitals, varying in size (smallest 138 beds, largest 880 beds) and geographical location. One internal medicine ward and one surgical ward of each hospital will participate in the study.

Nearly all hospitals in the Netherlands were initially invited to participate in the study, excluding specialised hospitals such as eye clinics and cancer hospitals, and hospitals already participating in a separate study related to the Frail Elderly Project. The hospitals that responded most quickly to the invitation were included in the study.

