### Study design

The study will be conducted using a stepped wedge cluster randomised trial design. The defining feature of this design is that the intervention will be introduced to all clusters -- or in this instance, hospitals -- in a sequential order [25,30,31]. At the start of the study in May 2011, no hospital will have access to the intervention, while at the end in March 2012 all hospitals will have been given access. This offers an advantage over parallel trials, in which certain hospitals would not receive the intervention. The e-learning course is expected to do more good than harm, making it unethical to withhold the intervention from participating hospitals [25,31].

After every monthly data collection moment, one or two new hospitals will receive access to the intervention, as illustrated in Figure 1. The start date at which each hospital is given access to the e-learning course will be randomly assigned, using simple or unrestricted randomisation. Hospitals will each be informed of the start date of the intervention prior to the start of the trial. After a period of 11 months, all 18 hospitals will have received the intervention, and the stepped wedge design will have resulted in gathered data from all hospitals for both the control and the intervention group. This offers an important methodological advantage: each hospital acts as its own control, thereby reducing contamination bias [31].

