### Data collection

Monthly patient record reviews of patients 70 years or older will be the main source of data. During 11 months, research nurses will review approximately 10 records per ward per month (20 per hospital), using both nursing and medical records. If a ward provides the research nurse with more than 10 records fitting the inclusion criteria, the nurse will take a random sample from the available records. All record reviews will take place within the same week of the month, using records of patients still in hospital or discharged during the previous week. From these records, data concerning provided delirium care will be gathered, which will offer the following information about the implementation of the delirium aspect of the Frail Elderly Project:

1. Detection of risk for delirium, as well as screening for falls, malnutrition, and physical impairment. The Frail Elderly Project has provided hospitals with screening instruments to assess these risks (Additional file 1). Alternative instruments that are used by hospitals are the Groningen Frailty Indicator [32] and the Identification of Seniors At Risk or ISAR [33].

2. Detection of delirium by nurses using the Delirium Observation Screening scale [34,35] (Table 1).

3. Diagnosis of delirium by physicians.

4. Prevention of delirium by nursing or medical interventions targeting common reversible causes of delirium.

5. Treatment of delirium by starting nursing or medical interventions targeting common reversible causes of delirium or by prescribing medication.

**Table 1 T1:** Delirium Observation Screening scale [34,35]

	The patient:	Never	Sometimes or always
1	Dozes during conversation or activities	0 points	1 point

2	Is easily distracted by stimuli from the environment	0 points	1 point

3	Maintains attention to conversation or action	1 point	0 points

4	Does not finish questions or answers	0 points	1 point

5	Gives answers which do not fit the question	0 points	1 point

6	Reacts slowly to instructions	0 points	1 point

7	Thinks to be somewhere else	0 points	1 point

8	Knows which part of the day it is	1 point	0 points

9	Remembers recent events	1 point	0 points

10	Is picking, disorderly, restless	0 points	1 point

11	Pulls IV tubes, feeding tubes, catheters etc.	0 points	1 point

12	Gets easily or suddenly emotional (frightened, angry, irritated)	0 points	1 point

13	Sees persons/things as somebody/something else	0 points	1 point

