### Research population

Records of patients admitted to the participating wards will be included in the study if the patient is 70 years or older and if the length of stay at the time of the record review is at least 24 hours. Only records of patients still in hospital at the time of the record review and patients discharged in the previous week will be included. A total of approximately 3,960 patient records will be reviewed in the course of the study.

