### Outcomes and data analysis

In the Frail Elderly Project hospitals are advised to screen all elderly patients directly after admission for the risk of developing or the presence of delirium, falls, malnutrition, or physical impairment. The e-learning course educates nurses on screening for delirium. The percentage of elderly patients that are indeed screened for the risk of delirium is the primary outcome of this study. Secondary outcome measures include: the percentage of elderly patients with an increased risk of delirium that are observed with the Delirium Observation Screening scale; the percentage of elderly patients with (an increased risk of) delirium that receive care aimed to prevent or treat delirium; and the percentage of elderly patients that are diagnosed with delirium. Covariates that will be used in the analysis are: age, gender, living situation, comorbidity [36], and admission diagnosis of the patients.

The data analysis will firstly consist of a comparison between hospitals that have received the intervention and hospitals that have not yet received the intervention, according to the stepped wedge schedule. This will be done using multilevel linear regression and multilevel logistic regression analyses. In these analyses, we will adjust for temporal trends and for clustering within hospitals using generalised estimating equations.

Different organisational or system factors that might influence adherence to the intervention or might lead to differences between hospitals in delivered care will be analysed. These factors include hospital type (academic, teaching, general), size, location (urban or rural), and type of records used (paper versus electronic).

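### Ward type is in neither the covariate list nor the clustering, although every hospital contributes one medical and one surgical ward: a small, conservative cost for the primary outcome, a possible ward-mix shift in two secondary outcomes

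*Protocol article*

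**What the plan says.** The Setting section of the protocol article fixes the ward structure: "One internal medicine ward and one surgical ward of each hospital will participate in the study". Under Data collection, sampling is by ward: "research nurses will review approximately 10 records per ward per month (20 per hospital"). A random sample is drawn only when a ward offers more than 10 eligible records. Study design makes the hospital the randomised unit, so both wards of a hospital change over together: "The start date at which each hospital is given access to the e-learning course will be randomly assigned".

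Outcomes and data analysis announces multilevel linear and logistic regression and states: "we will adjust for temporal trends and for clustering within hospitals using generalised estimating equations". The adjustment set is: "Covariates that will be used in the analysis are: age, gender, living situation, comorbidity [36], and admission diagnosis of the patients". A separate list of organisational factors does not mention ward either: "These factors include hospital type (academic, teaching, general), size, location (urban or rural), and type of records used (paper versus electronic").

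The primary outcome and one secondary outcome (delirium diagnosed) are percentages of all sampled elderly patients. The other two secondary outcomes have restricted denominators: DOS use among patients at increased risk, and preventive or curative care among patients with delirium or at increased risk.

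**The concern.** Ward type is set by the design, costs nothing to record, and plausibly relates to the outcomes. The article's Background reports delirium in about 25% of hospitalised patients aged 65 and over, and up to 62% in surgical patients. Its Discussion warns that record quality may differ between hospitals or wards. The analysis text deals with the hospital half of that warning only.

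Two consequences need checking:

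- **Precision.** A model with hospital as its only level treats a stable difference between a hospital's two wards as noise between patients, which affects its model-based standard errors.
- **Ward mix.** Where the denominator is not all sampled patients, the wards' shares in it can change when the course is introduced. A pooled percentage could then move although care within each ward type stays the same.

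**Working it through.** **The plan's own count.** 36 wards × 10 records × 11 months = 18 × 20 × 11 = 3,960, which agrees with the article: "A total of approximately 3,960 patient records will be reviewed in the course of the study". If every ward delivers 10 records each month, ward type is balanced between control and intervention months for outcomes measured on all sampled patients.

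**Primary outcome, linear scale.** The article gives no ward variance or ward difference, so these are assumed. Total variance is 0.4 × 0.6 = 0.24 (from the 40% baseline), hospital variance σ²h = 0.012, ward variance σ²w and ward-type gap g. Stable ward effects leave a patient-level variance of σ²e = 0.24 − σ²h − σ²w − g²/4. A hospital-only model works instead with about σ²e + σ²w/2 + g²/4. The approximate ratio of model-based to true SE is the square root of the second over the first. The exact generalised least squares values use 18 hospitals, 11 months and one or two hospitals starting per step (the figure is not shown, so the order is assumed):

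| σ²w | g | σ²e | Approximate ratio | Exact, hospital only: model SE, true SE, ratio | Ratio with ward type | Ratio with ward type and ward level |
|---|---|---|---|---|---|---|
| 0.012 | 0 | 0.216 | √(0.222/0.216) = 1.014 | 0.02570, 0.02537, 1.013 | 1.013 | 1.000 |
| 0.012 | 0.2 | 0.206 | √(0.222/0.206) = 1.038 | 0.02570, 0.02480, 1.037 | 1.014 | 1.000 |
| 0.024 | 0.2 | 0.194 | √(0.216/0.194) = 1.055 | 0.02549, 0.02420, 1.053 | 1.030 | 1.000 |
| 0.024 | 0.4 | 0.164 | √(0.216/0.164) = 1.148 | 0.02549, 0.02231, 1.142 | 1.035 | 1.000 |

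Moderate assumptions therefore give about 1-6%. The 14% needs a 40-point gap between ward types. The true SE hardly changes when ward enters the model (0.02420 against 0.02419 in the third row). With equal counts, what is lost is the accuracy of the stated SE, not real precision. With uneven or sparse counts the real gain is about 0.4-6%, again under assumed counts.

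**Primary outcome, logit scale.** 400 simulated trials per setting were analysed by logistic GEE with exchangeable hospital clusters:

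- Ward log-odds difference 0.8: coefficient 0.70 without ward type and 0.73 with it; model SE 0.107 and 0.109; mean z 6.58 and 6.70.
- Difference 1.6: coefficient 0.63 and 0.72; model SE 0.107 and 0.113; mean z 5.91 and 6.30.

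Here the SE does not shrink when ward type is added; the coefficient grows. Model SE over empirical SE is 1.02 and 1.05 without ward type, and 1.00 and 0.99 with it. An SD from 400 trials carries a relative error of about 1/√800 = 3.5%, so these ratios show direction at best.

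**When ward effects are not stable.** Adding ward-by-month variance of 0.006 or 0.012 to the second row of the table turns the hospital-only ratio into 0.93 or 0.85, so the SE is now too narrow. With ward type and a ward level it is 0.89 or 0.82. Ward terms do not cure this, which is why robust hospital-level errors should stay.

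**Ward mix in the two restricted outcomes.** Shift = ward difference × change in ward share. If the surgical share goes from 50% to 55-70% and the ward types differ by 10-30 points, the smallest shift is 10 × 0.05 = 0.5 points and the largest is 30 × 0.20 = 6 points. If the mix is constant, the shift is 0.

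An example assumes equal records per ward, at-risk patients in proportion to those screened, and no patient covariates. Screening rises from 30% to 60% in surgical wards and from 50% to 60% in medical wards, while DOS use stays at 40% and 60%. The surgical share goes from 0.30/0.80 = 37.5% to 0.60/1.20 = 50%. Pooled DOS use goes from 0.375 × 40 + 0.625 × 60 = 52.5% to 0.5 × 40 + 0.5 × 60 = 50.0%, with no change in either ward type.

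**The case against.** The strongest reply has four parts.

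- **Admission diagnosis is already a covariate**, and with one medical and one surgical ward per hospital it partly stands in for ward type. This stands. The figures above contain no patient covariates, so they are upper-side illustrations.
- **GEE clustered on the hospital is valid**, because the hospital is the randomised unit and its robust errors already cover correlation within wards. This also stands, apart from small-sample bias with 18 clusters.
- **Little power is at stake.** At the planned change from 40% to 60%, a standard stepped-wedge calculation gives power above 0.999 for any ICC from 0 to 0.9999, with or without ward. This stands too. The article's own 0.8 rests on an ICC of 1.0, a separate matter.
- **An article may leave nesting levels to a fuller document.** This stands in part: the word multilevel does not exclude a ward level. But the covariate list is worded as the set to be used, and it omits a design factor. That makes this a choice to improve, not a missing detail.

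A reader might infer that the primary test is invalid, that standard errors are always too wide, or that every secondary outcome is affected. The article supports none of these. With stable ward effects the error is conservative. On the logit scale it appears in the coefficient, and ward-by-month variation reverses the SE direction. Delirium diagnosis, like the primary outcome, uses all sampled patients, so its ward mix moves only if a ward falls short of 10 records.

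**Conclusion.** The point holds as a minor one. The stated model leaves out ward type although the design builds it in.

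For the primary outcome this costs about 1-6% in model-based SE on the linear scale, or a somewhat attenuated coefficient and lower z on the logit scale. Both figures assume stable ward effects and assumed ward differences. With hospital-level robust errors and exactly 10 records per ward, no real precision is lost.

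The more substantive part concerns DOS use and preventive or curative care, where a change in ward mix could move the pooled percentage by an assumed 0.5-6 points before adjustment for admission diagnosis. To be mistaken for an effect of the course, the change must follow access to it and not only calendar time, because temporal trends are adjusted for. That could happen if increased risk is known mainly from the recorded screening the course is meant to raise. The article does not say how it is established, so this remains an assumption.

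**What to change.** In Outcomes and data analysis, add ward type (internal medicine or surgical) as a fixed covariate for the primary and all other record-based outcomes. Where a mixed model is used, add ward as a level nested in hospital. Keep hospital as the top cluster, with hospital-level robust standard errors and a small-sample correction for 18 clusters.

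The cost is a sentence or two of analysis wording. Records are sampled by ward, so the variable should already be at hand, and no new data are needed.

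The change removes only the between-ward part of a mix shift. It does not cure selection into the at-risk denominators within a ward, nor ward-by-month variation; for the latter, the robust errors provide the protection.

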### Sampling

The power calculation for the part of the study focused on the effect of e-learning for nurses on provided care (*i.e*., screening for delirium risk) resulted in a power of 0.8, based on the following assumptions: 18 hospitals (36 wards); an improvement of delirium risk screening of 20% (from having 40% of the elderly patients screened to 60%) after the e-learning introduction; an alpha of 0.05; a total of 360 patient records for reviewing per month; an intracluster correlation coefficient (ICC) of 1.0.

For the aspect of the study focused on the effect of e-learning on knowledge, we expect a power of 0.99 assuming the study is conducted in 36 wards (18 hospitals), with an e-learning effect size of 1.00 [22], an alpha of 0.05, at least 30 nurses per ward, and an intraclass correlation of 0.20. When adjusting the effect size to 0.5, a power of at least 0.8 is still achieved.

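### The primary analysis is described as both multilevel logistic regression and GEE, which give different odds ratios; one must be named, with inference suited to 18 hospitals

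*Protocol article*

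**What the plan says.** Two consecutive sentences in Outcomes and data analysis describe how hospitals with and without the e-learning course will be compared. The first reads: "This will be done using multilevel linear regression and multilevel logistic regression analyses". The second reads: "In these analyses, we will adjust for temporal trends and for clustering within hospitals using generalised estimating equations". The article does not say which of the two will produce the primary result.

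The primary outcome is the percentage of elderly patients screened for delirium risk, so each record contributes a yes or a no. The listed secondary outcomes are also percentages of patients.

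The hospital is the unit of randomisation: "the intervention will be introduced to all clusters -- or in this instance, hospitals -- in a sequential order". There are 18 hospitals, and within them "One internal medicine ward and one surgical ward of each hospital will participate in the study". The Sampling section sets "an alpha of 0.05; a total of 360 patient records for reviewing per month", and it plans for an improvement "from having 40% of the elderly patients screened to 60" per cent.

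**The concern.** A multilevel logistic model handles clustering through random effects, and its odds ratio compares patients within the same hospital. GEE handles clustering through a working correlation and a robust variance, and its odds ratio compares averages over all hospitals. A multilevel logistic model is not adjusted for clustering by means of GEE. With a binary outcome the two odds ratios differ whenever hospitals differ.

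Two things are at stake. First, the text would allow either model to be presented as the planned analysis after the results are known, and the reported odds ratio would change with the choice. Second, the two models go wrong in different ways in a trial with 18 clusters and 11 months. The ordinary sandwich variance is too small when clusters are few. A random hospital intercept alone ignores any drift of a hospital from month to month. Such drift is plausible here: the Background leaves implementation of the Frail Elderly Project to each hospital, and the Discussion describes a changing context and an unmeasured starting level that may differ between hospitals.

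**Working it through.** **Inputs from the protocol article.** 18 hospitals, 11 monthly measurements, 20 records per hospital per month (18 × 11 × 20 = 3,960, as stated), alpha 0.05 (taken as two-sided), 40% versus 60% screened. One or two hospitals start after each measurement. With 10 gaps between 11 measurements, this implies eight steps of two hospitals and two of one (8 × 2 + 2 × 1 = 18). That gives 107 exposed and 91 unexposed hospital-months out of 198.

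**The plan's own figure.** The article gives no error rate beyond the nominal 5%, so the figure to reproduce is the power of 0.8. With "an intracluster correlation coefficient (ICC) of 1.0", the design effect for 20 records is 1 + 19 × 1.0 = 20, and 3,960 / 20 = 198 effective observations. A two-proportion test of 40% versus 60% with 99 per arm has power 0.808, or 0.806 with the 91:107 split. So 0.8 is reproduced, but only by treating each hospital-month as one independent observation. It supplies no usable variance component for the primary outcome. The ICC of 0.20 in the same section concerns nurses' knowledge. The variance components below are therefore assumptions.

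**Size of the gap between the two odds ratios.**
- Marginal odds ratio: (0.6 / 0.4) / (0.4 / 0.6) = 2.25, log 0.811.
- Usual approximation: conditional log OR ≈ marginal log OR × √(1 + 0.346 σ²), with σ² = 3.29 × ICC / (1 − ICC) on the latent scale.
- ICC 0.1: σ² = 0.366, factor 1.061, conditional OR = exp(0.861) ≈ 2.36.
- ICC 0.3: σ² = 1.410, factor 1.220, conditional OR = exp(0.989) ≈ 2.69.

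The same effect would thus be reported as 2.25 or as about 2.36-2.69.

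**Rejection rate with no effect.** The schedule was simulated with 40% screened at baseline. Assumed SDs on the logit scale: hospital 0.4-0.8, ward 0-0.5, hospital-by-month 0-0.5, ward-by-month 0-0.4, hospital slope 0-1.0 over the study. There were 3,000 runs per scenario for GEE (Monte Carlo error about 0.5 points) and 1,500 for the mixed model.

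| Analysis | Rejects at nominal 5% |
|---|---|
| GEE by hospital, ordinary sandwich, z-test | 7.3-9.4% |
| Same, t on 16 df | 5.6-7.5% |
| GEE, Kauermann-Carroll, t on 16 df | 4.5-6.3% |
| GEE, Mancl-DeRouen, t on 16 df | 3.5-4.9% |
| Random hospital intercept, likelihood-ratio test; hospital effect only | 7.0% |
| Same, ward effects added to the data | 6.1% |
| Same, hospital-by-month SD 0.3 | 9.6% |
| Same, hospital-by-month SD 0.5 | 16.3% |

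Two further simulations of the schedule gave 8.0-8.8% and 7.7-8.9% for uncorrected GEE. Near 40% screened, a logit SD of 0.3 is about 0.3 × 0.4 × 0.6 = 7 percentage points of month-to-month movement within a hospital, and 0.5 is about 12 points.

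**Ward level.** Adding constant ward effects to the data moved uncorrected GEE from 8.7% to 9.1% and the mixed model from 7.0% to 6.1%. Neither is a material increase.

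**The case against.** The strongest reply is that this is a condensed article. The variance estimator, small-sample correction, reference distribution and list of random effects commonly sit in an analysis plan or full protocol that is not shown. Nothing printed rules out a correction. That stands, and the absence of these details is not counted as an error here. It does not settle the main point, because the article names both methods itself.

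A second reply is that the authors may use multilevel loosely for any clustered regression, with GEE as the actual method. That is possible, and for a linear model both approaches target the same mean difference. But the primary outcome is binary, and a reader cannot tell from the text which odds ratio is meant.

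Three stronger readings are tempting and are not supported:

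- A reader might infer that the test will run at about 8-15%. Uncorrected GEE never exceeded 9.4%. Rates of 10% and above need an analysis that leaves sizeable hospital-by-month variation unmodelled, and the article gives no figure for that variation.
- A reader might infer that leaving out a ward level inflates the error. The hospital is randomised, both wards switch together, and a hospital-level robust variance already covers correlation within and between its wards. The simulations agree.
- A reader might extend the rates to every secondary outcome. Two of these are restricted to patients at risk or with delirium, so they have fewer records per cell, and they were not simulated.

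**Conclusion.** The point holds as a contradiction in the stated primary analysis: two models are named for one comparison, and for a binary outcome they estimate different odds ratios. At the planned effect the gap is 2.25 against about 2.36-2.69, for an assumed latent-scale ICC of 0.1-0.3.

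The error rates show why the choice matters; they are not properties of the printed text. With 18 hospitals, plain GEE with a z-test would reject at roughly 7-9%. A random-hospital-intercept model would reject at about 6-7% without hospital-by-month variation, and at about 10-16% only if that variation has a logit SD of 0.3-0.5. A corrected GEE stays at about 3.5-6%. All of these rest on the inferred step pattern, 20 records in every hospital-month and the assumed variance components. The matter should be put right, and doing so needs no change to the design or to data collection.

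**What to change.** Name one primary model in Outcomes and data analysis and state which odds ratio it estimates. One suitable choice is logistic GEE clustered by hospital, with month as a factor, a Kauermann-Carroll or Mancl-DeRouen variance, and a t reference on about 16 degrees of freedom (18 hospitals − 2). Report the multilevel logistic model as a sensitivity analysis.

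If the mixed model is preferred as primary, include a hospital-by-month random effect and a small-sample reference distribution, and report GEE as the sensitivity analysis.

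The cost is a change of wording and slightly wider confidence intervals. The t reference alone widens them by 2.120 / 1.960 = 1.08, and the corrected variance adds somewhat more. Power for the planned effect should be little affected. In a Hussey-Hughes calculation with an assumed ICC of up to 0.20, power was at least 0.99, whether the hospital effect was constant over time or all the correlation lay within hospital-months. The largest standard error there was 0.0466, so 0.20 / 0.0466 − 2.120 = 2.17, which still corresponds to power of about 0.985 before the variance correction.
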